## Abstract

**Background:**

Attention-deficit/hyperactivity disorder (ADHD) is a common neurological disorder affecting 5 % of children worldwide. A prevalent problem for children with ADHD is initial insomnia. The gold standard treatment to manage ADHD symptoms is stimulant medications, which may exacerbate the severity of existing initial insomnia. Currently, no gold standard treatment option exists for initial insomnia for these children. Melatonin, a hormone and a popular natural health product, is commonly provided to children by parents and recommended by healthcare providers, but high quality pediatric evidence is lacking.

**Methods/design:**

This trial is a multicenter randomized triple-blind, placebo-controlled, parallel-group, randomized, controlled trial (RCT), in which each participant is offered an N-of-1 trial. An N-of-1 trial is a multiple-crossover, randomized, controlled trial conducted in a single individual. For the N-of-1 trial, each participant will undergo three pairs of treatment/placebo periods; each period is 1 week in length. Half the participants will have melatonin in the first period, the other half will start with placebo, and this will make up the parallel-group RCT. The primary outcome will be mean difference in sleep onset latency as measured by sleep diaries. A comparison of treatment effects yielded by the RCT data versus the aggregated N-of-1 trial data will also be assessed.

**Discussion:**

This trial will provide rigorous evidence for the effectiveness of melatonin in children with ADHD on stimulants who experience initial insomnia. Further, this study will provide the first prospectively planned head-to-head comparison of RCT data with pooled data from a series of N-of-1 trials. Aggregated N-of-1 trials may be a powerful tool to produce high quality clinical trial evidence.

**Trial registration numbers:**

ClinicalTrials.gov, NCT02333149. Registered on 16 December 2014. Australian New Zealand Clinical Trials Registry, ACTRN12614000542695. Registered on 21 May 2014.

**Electronic supplementary material:**

The online version of this article (doi:10.1186/s13063-016-1499-6) contains supplementary material, which is available to authorized users.

## Background

Attention-deficit/hyperactivity disorder (ADHD) is the most common neurodevelopmental disorder in children [1, 2] affecting 5–13 % of Canadian, Australian, and American school-aged children [3, 4]. ADHD is characterized by inattention, hyperactivity, and impulsivity, which negatively interfere with the child’s socialization and education. It has long-term ramifications throughout adulthood [5], leading to an academic underachievement, language and literacy problems, fewer years of completed schooling, lower-ranking employment, and lower achieved social class than control groups [6–11]. The utilization and cost of healthcare services for children with ADHD in the United States are approximately double those for children without ADHD. Pelham and colleagues reported that in 2005, the societal cost of childhood ADHD was approximately $42.5 billion USD [12, 13].

The first line of treatment for ADHD is stimulant medication, which is effective in 70–90 % of school-aged children [14–16]. The most commonly prescribed stimulants, methylphenidate, and amphetamines experienced a fivefold increase in use from 1987 to 2002 among children in the United States [17]. Similarly, between 1990 and 2000, Australia saw a fivefold increase in the number of children and adolescents with ADHD who had commenced taking stimulant medication [18]. Although stimulants help to effectively manage ADHD symptoms, they are also associated with a number of adverse events: initial insomnia is among the most commonly reported, and is characterized by prolonged sleep onset latency (SOL).

In general, sleep problems are among the most common complaints in childhood, with a prevalence of 6 %, as reported by parents [19]. In comparison, 50–60 % of children with ADHD experience sleep problems [20]; when children with ADHD are treated with stimulant medication, the prevalence of initial insomnia increases to 64–70 % [21]. Sleep problems not only have negative impacts on a child’s social, physical, and mental well-being [20], but lead to exhaustion and high stress levels in parents [22].

### Treatment of insomnia

Nonpharmacological interventions such as improving sleep hygiene are generally preferred as first-line treatment. Sleep hygiene entails a variety of strategies to promote the quantity and quality of sleep, such as avoiding strenuous play/exercise before bed; going to bed at a consistent time in a quiet, dark room; establishing consistent waking times; getting regular physical exercise; and maintaining a regular daily routine [23]. Although it is considered the first line of treatment, preliminary research suggests sleep hygiene has limited effectiveness in pediatric ADHD [24]. Weiss and colleagues found that sleep hygiene on its own only helped a small fraction (15 %) of children with ADHD [22].

The use of pharmacological agents to promote sleep is common, but evidence regarding safety and effectiveness for pediatric use is lacking [20]. Children with ADHD are more likely to be prescribed medications with hypnotic properties such as clonidine or antihistamines to promote sleep; however, the safety and effectiveness for this off-label use have not been established in children [25]. At present, no approved medications exist for childhood insomnia in Canada or Australia [26]. In the absence of approved pharmacotherapy, Canadian and Australian healthcare providers recommend the most popular natural health product (NHP) for sleep: melatonin [27].

### Melatonin

First discovered in 1958 [20], melatonin is a hormone released by the pineal gland and regulates the sleep-wake cycle [28, 29], thermoregulatory cycle [30], reproductive rhythm [31], and immune function [32]. Its secretion follows a circadian rhythm that is entrained to the light/dark cycle and is regulated by the hypothalamic suprachiasmatic nucleus (the central pacemaker of the body) [28]. The secretion of melatonin is suppressed by daylight but increases with darkness; it regulates the circadian rhythm by promoting the desire to sleep at night [28]. Individuals with neurodevelopmental disorders often have biological clock or circadian rhythm disturbances, which result in sleep disorders [29]. Children with ADHD have a delayed endogenous circadian pacemaker as measured by delayed sleep onset, dim-light melatonin onset, and time of awakening [33–35]. These findings suggest that melatonin may be particularly effective in children with ADHD to help promote sleep onset by two possible routes: as a chronobiotic and as a hypnotic.

Classified as an NHP by Health Canada (HC), melatonin is available over the counter [36]. In Australia, melatonin may be obtained with a prescription or without, by ordering it through the internet. Melatonin is widely used in pediatric populations for the treatment of sleep disorders [37]. A 2003 survey of 671 US community-based pediatricians reported that approximately 25 % of physicians recommended melatonin for sleep problems in toddlers (1–8 %) and adolescents (15–19 %) [26]. A 2013 study conducted in Australia found that melatonin was prescribed 89.1 % of the time for poor sleep initiation in children by general pediatricians [27].

Members of our team conducted a systematic review on the efficacy of melatonin for the treatment of sleep disorders in an evidence report for the Agency for Healthcare Research and Quality in 2004 [28]. We identified six trials of adults and children reporting SOL who had a secondary sleep disorder; meta-analysis favored melatonin but was nonsignificant (-13.2 min; 95 % CI: -27.3, 0.9) [38]. Our systematic review findings were limited by too few studies of inadequate sample sizes (n = 7–30). A more recent review identified four studies investigating the use of melatonin for insomnia in children [20]. These studies included an open-labeled study, two randomized controlled trials (RCTs) and one 3-year follow-up study [22, 39, 40]. All studies showed significant improvement in SOL in the treatment arms; however, the trials were limited by small sample sizes, variable SOL criteria, ADHD criteria, and treatment assessments, and a lack of generalizability.

### N-of-1 Trials

A major barrier to the conduct of RCTs of NHPs is participant access to the study product without a prescription (personal communication, National Center for CAM, US National Institutes of Health). Since melatonin is readily available in Canada, parents may (1) prefer to buy it themselves instead of risking their child being randomized to a placebo control arm or (2) contaminate an RCT by administering nonstudy melatonin to their child. An ideal alternative to an RCT is an N-of-1 trial, defined as a prospective, multiple-crossover, placebo-controlled, triple-blind, randomized trial in a single subject. In an N-of-1 trial, each participant is assured of receiving both the study medication and placebo, and thus learns whether the treatment works specifically for them or not.

Melatonin is an optimal treatment for testing within an N-of-1 trial framework for several reasons: (1) it has a short half-life (0.54–2 h) [28]; (2) no residual impact remains on the target symptom after excretion [38]; and (3) it is being used to treat an important and recurrent symptom that has a negative impact on quality of life and compliance with ADHD stimulant treatment [22].

### Why is this trial needed now?

More than 1000 controlled clinical trials have evaluated melatonin for the treatment of sleep disorders [28], but the literature for children with ADHD is limited to very few studies confounded by small sample sizes and limited clinical applicability [20]. The fact that melatonin is being widely used in this population despite the absence of high-quality clinical evidence highlights the need for a well-designed RCT. Our proposed study will overcome the recurring limitations of small sizes in pediatric trials by adequately powering the parallel-group trial and offering each participant an N-of-1 trial to promote trial enrollment. To our knowledge, this will be the first prospectively planned head-to-head comparison of parallel group RCTs and N-of-1 trials.

### Objectives

The primary objectives of this study are to (1) determine the effectiveness of weight-based dosing of melatonin for initial insomnia (i.e., reducing sleep onset latency) in children and adolescents with ADHD who are receiving stimulant medication and (2) determine whether N-of-1 trials provide similar estimates of treatment effect to parallel group RCTs.

## Methods/design

### Study design

We will conduct a prospectively planned, head-to-head comparison of a parallel-group RCT design with aggregated N-of-1 trial data. The trial is a multicenter, randomized, triple-blind, placebo-controlled series of N-of-1 trials with an embedded RCT. Half the participants will be randomly allocated to melatonin in the first period; the other half will start with placebo; and the RCT will include the data from the first period only. For the N-of-1 trial, each participant will undergo three pairs of treatment/placebo periods (each period is 1 week long, and each N-of-1 trial will last a total of 6 weeks). See Fig. 1 for scheme of the study design, Fig. 2 for flow of participants through study, and the SPIRIT checklist (Additional file 1).

**Fig. 1 Fig1:**
[figure not shown]
Scheme of study design

**Fig. 2 Fig2:**
[figure not shown]
Flow of participants through study

### Study setting

The trial sites will be outpatient pediatric and/or family medicine clinics at hospital and community clinics in Australia and in Edmonton, Canada. Staff in all relevant clinics will be informed about the availability of the trial and will refer participants to the study investigators at each site. Community patients will also be able to be referred by their physician.

### Study participants

To be included in the trial, participants must (1) be between the ages of 6 to 17 years; (2) have a diagnosis of ADHD according to the DSM-IV criteria; (3) be on a stable dose of stimulant medication for at least 1 month prior to the study; and (4) have an SOL of ≥ 45 min, ≥ 3 nights/week, for ≥1 month. Exclusion criteria include (1) children with comorbid psychiatric/neurological diagnosis that may affect sleep; (2) children with untreated obstructive sleep apnea, untreated sleep-related breathing disorder, untreated narcolepsy, sleep-related movement disorders, parasomnias, adjustment insomnia, insomnia due to drug use or mental health issues, or secondary enuresis; (3) children with a known allergy or hypersensitivity to melatonin or other study drug ingredients; (4) children on immunosuppressive drugs, blood pressure drugs, selective serotonin reuptake inhibitors or anticoagulant drugs; and (5) children not on a regular sedative/hypnotic medication, whose parents do not agree not to alter the daily dose of these for the duration of the trial; children with active or uncontrolled disorders (hormonal disorders, diabetes, liver disease, abnormal kidney function, untreated kidney disease or blood clotting disorders); (6) children with seizure disorders; (7) breastfeeding or pregnant women; (8) female participants with child-bearing potential not practicing an acceptable form of birth control throughout the trial (in Australia, females who are ≥ 12 years who are menstruating and sexually active); (9) participants who disagree to not driving or operating heavy machinery within 8 hours of ingestion of study medication; and (10) children whose parent/primary caregiver does not understand English, have a phone, or provide informed consent.

## Interventions

### Sleep-hygiene phase

Upon recruitment, all participants/parents will receive an information sheet and a 15-min counseling session to review optimal sleep hygiene. The family will be asked to try the sleep-hygiene strategies suggested for 14 days. At day 7, the research assistant will telephone the family to ensure that sleep hygiene measures are implemented and address any barriers. If the child is still eligible for the study at day 14, the child will be offered enrollment into the trial. While sleep hygiene is an important first step, preliminary data suggest that only 15 % of children will respond [22]. Therefore, the majority of those pre-enrolled are anticipated to continue on to trial enrollment. Randomization will not occur until trial enrollment.

### Melatonin

Previous research suggests that an oral dose of 2.5–10 mg before or at the desired bedtime is well tolerated in children [41]. Similar to previous pediatric trials [40], we will use weight-based dosing, giving 3 mg of sublingual melatonin to those children who are < 40 kg and 6 mg to those ≥ 40 kg. Melatonin will be taken once daily, 30 minutes prior to bedtime. Placebo with an identical appearance has been manufactured. The clinical effect of melatonin is rapidly evident, and melatonin has a short half-life (0.54–2 h). Therefore, an appropriate duration of each treatment period is 1 week. Data from day 1 of each period will be discarded to provide a washout period. If a carryover effect is found subsequent to day 1, appropriate adjustments will be made, e.g., discarding an extra day’s data.

### Randomization

Participants will undergo three pairs of treatment with melatonin and placebo. In each pair, the order of treatment will be randomized. In particular, the first period for each patient will be randomized in variable block sizes of 4 and 6, stratified by age (<12 and ≥ 12 years) and country (Canada or Australia), to ensure a balance of the treatment groups for the parallel-group RCT. The randomization code will be developed by the study statistician. The randomization code will be provided to the central research pharmacy for each participating site and to maintain the blind. When a participant has been enrolled, the research pharmacy will randomize the subject based on the master randomization list and courier six bottles numbered 1–6, corresponding to each week’s treatment. Each bottle will contain seven capsules (or 14 for children who weigh < 40 kg) to be taken over 7 days. Randomization codes will be kept by the research pharmacy in case the code needs to be broken for safety reasons as determined by the Data Safety and Monitoring Board (DSMB).

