### Blinding

The trial will be triple-blinded (participant, healthcare provider, and statistician). The placebo has the same appearance, volume, weight, odour, and taste as the active product. There will be unblinding of the individual participant’s randomized N-of-1 sequence for the healthcare provider and participant only upon receiving individual trial reports or on participant request to stop the trial early.

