### Trial status

Recruitment began in March 2015.

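### The capsule counts in Randomization run opposite to the weight-based dose in Melatonin, so no single capsule strength gives both weight bands the planned dose

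*Protocol article*

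**What the plan says.** Two sections of the protocol article, both under Interventions, bear on the dose.

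- **Melatonin** sets the dose by weight, "giving 3 mg of sublingual melatonin to those children who are < 40 kg and 6 mg to those ≥ 40 kg", and its frequency: "Melatonin will be taken once daily, 30 minutes prior to bedtime".
- **Randomization** describes the supply. On enrolment, "the research pharmacy will randomize the subject based on the master randomization list and courier six bottles numbered" 1 to 6, one for each week. Of their contents it says: "Each bottle will contain seven capsules (or 14 for children who weigh < 40 kg) to be taken over 7 days".

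The article gives no capsule strength. It mentions neither a second strength nor dummy capsules. The Blinding section refers to one product: "The placebo has the same appearance, volume, weight, odour, and taste as the active product". The first primary objective is to "determine the effectiveness of weight-based dosing of melatonin for initial insomnia", and the Trial status section reports: "Recruitment began in March 2015".

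**The concern.** The dose rule and the bottle rule point in opposite directions. Under the first, the heavier child receives twice the melatonin of the lighter child. Under the second, the lighter child receives twice the capsules. If all active capsules have the same content, these cannot both be followed.

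The sentence at fault says what the research pharmacy puts in each child's bottle, in a pediatric drug trial. If it were followed with one capsule strength, at least one weight band would receive a dose other than the stated one. The treatment effect would then describe a different regimen from the one named in the first primary objective. The Aggregated analysis section also lists dose among the factors for secondary modelling, and that analysis would carry wrong dose labels. Even if the trial was run correctly, a reader who wants to repeat, pool or apply it cannot reconcile the regimen from the article.

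**Working it through.** **Inputs**

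- Planned daily dose: 3 mg (< 40 kg) and 6 mg (≥ 40 kg), once daily (Melatonin).
- Capsules per 7-day bottle: 14 (< 40 kg) and 7 (all others) (Randomization).
- Capsule strength *s*: not stated, so treated as unknown.

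**Step 1. Can the planned doses be reproduced from the bottle contents?**

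Daily dose = (capsules per bottle ÷ 7) × *s*.

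- < 40 kg: 14 ÷ 7 = 2 capsules a day, so 2*s* mg. This equals 3 mg only if *s* = 1.5 mg.
- ≥ 40 kg: 7 ÷ 7 = 1 capsule a day, so *s* mg. This equals 6 mg only if *s* = 6 mg.

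Weekly totals agree. An active bottle must hold 3 × 7 = 21 mg or 6 × 7 = 42 mg, so the strengths needed are 21 ÷ 14 = 1.5 mg and 42 ÷ 7 = 6 mg. No common strength exists. The lighter-to-heavier dose ratio is 3 ÷ 6 = 0.5 as planned, but 2 ÷ 1 = 2.0 from the printed counts at one strength.

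**Step 2. Size of the error at a single strength**

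Dispensed ÷ planned dose is 2*s* ÷ 3 for < 40 kg and *s* ÷ 6 for ≥ 40 kg.

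| Assumed *s* | < 40 kg: dispensed (planned 3 mg/day) | Ratio | ≥ 40 kg: dispensed (planned 6 mg/day) | Ratio |
|---|---|---|---|---|
| 1.5 mg | 3 mg | 1.0 | 1.5 mg | 0.25 |
| 3 mg | 6 mg | 2.0 | 3 mg | 0.5 |
| 6 mg | 12 mg | 4.0 | 6 mg | 1.0 |

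At any other single strength both bands are wrong. The Melatonin section cites 2.5–10 mg as well tolerated. The swapped doses at 3 mg stay inside that range. The 12 mg/day at *s* = 6 mg lies above it.

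**Step 3. What if the sign is reversed?**

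With 7 capsules for < 40 kg and 14 for ≥ 40 kg, the strengths needed are 21 ÷ 7 = 3 mg and 42 ÷ 14 = 3 mg. One strength then serves both bands and gives 3 and 6 mg a day, exactly as the Melatonin section states. This agreement is the main reason to think that < was printed for ≥.

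**The case against.** The strongest reply is that Randomization gives capsule counts, not milligrams, so the conflict depends on a single strength. With 1.5 mg capsules for lighter children and 6 mg capsules for heavier ones, both sections hold. That cannot be excluded, and the singular wording in Blinding fits one strength without proving it. But two strengths in a 1:4 ratio, with the smaller dose split over more capsules, would be an odd arrangement, and the article does not mention it. If it were true, the text would still need a sentence saying so.

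Second, the intended regimen in milligrams is stated clearly in one place, and the faulty text is a parenthesis about packaging, probably a one-character slip. This is fair. It makes the point a correction and not a criticism of the design.

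Third, the article condenses a fuller protocol, and nothing shows that the pharmacy worked from this sentence. This also stands: actual misdosing is not shown. An article may leave capsule strength to the full protocol, so its absence alone would not be a finding. It matters here only because it would settle the conflict.

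Finally, the stated counts depend on weight and not on treatment, so the slip by itself does not unblind or bias the comparison of melatonin with placebo. That is correct. If doses were really swapped, what changes is the dose that the effect describes.

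**Conclusion.** The concern holds. As printed, the bottle contents and the weight-based dose cannot both be right at any single capsule strength. At 3 mg, the likeliest strength, each child's dose would be wrong by a factor of two and the two bands exactly swapped. At 1.5 mg the heavier band would get a quarter of its dose, and at 6 mg the lighter band four times its dose.

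This rests on one assumption, that a single strength was made. The 3 mg figure is inferred from the fact that reversing the sign brings both bands to it. A reversed inequality sign is the probable cause. Randomization, sample size, power and type I error are unaffected. The correction should be made because the sentence is a dispensing rule for children in a trial that is already recruiting.

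**What to change.** 1. Have the sponsor confirm the capsule strength and state it.
2. If there is one strength of 3 mg, change < to ≥ in the bottle sentence under Randomization. A clear wording would be: weekly bottles hold 7 capsules for children under 40 kg and 14 for children of 40 kg or more; each active capsule contains 3 mg of melatonin.
3. If 1.5 mg and 6 mg capsules were really made, keep the counts and state both strengths with their weight bands.
4. As recruitment has begun, compare pharmacy dispensing counts with each child's weight band. Only if bottles went out reversed, inform the DSMB and report the effect for the dose actually given.

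The cost is one corrected sign, one stated strength and one check of dispensing records. No new data, visits or change in sample size are needed.
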